#### *Carcinogenesis, Mutagenesis, Impairment of Fertility*

Long-term studies in animals with Vivotif® have not been performed to evaluate carcinogenic potential, mutagenic potential or impairment of fertility.

#### *Pregnancy*

##### *Category C*

Animal reproduction studies have not been conducted with Vivotif®. It is not known whether Vivotif® can cause fetal harm when administered to pregnant women or can affect reproduction capacity. Vivotif® should be given to a pregnant woman only if clearly needed.

#### *Nursing Mothers*

There is no data to warrant the use of this product in nursing mothers. It is not known if Vivotif® is excreted in human milk.

#### *Pediatric Use*

The safety and efficacy of Vivotif® has not been established in children less than 6 years of age. This product is not indicated for use in children less than 6 years of age.

### **Dosage and Administration**

One capsule is to be swallowed approximately 1 hour before a meal with a cold or lukewarm [temperature not to exceed body temperature, e.g., 37 °C (98.6 °F)] drink on alternate days, e.g., days 1, 3 and 5. Immunization (ingestion of all 3 doses of Vivotif®, Typhoid Vaccine Live Oral Ty21a) should be completed at least 1 week prior to potential exposure to *S. typhi*.

The blister containing the vaccine capsules should be inspected to ensure that the foil seal and capsules are intact. The vaccine capsule should not be chewed and should be swallowed as soon after placing in the mouth as possible. A complete immunization schedule is the ingestion of 3 vaccine capsules as described above.

#### *Re-immunization*

The optimum booster schedule for Vivotif® has not been determined. Efficacy has been shown to persist for at least 5 years. Further, there is no experience with Vivotif® as a booster in persons previously immunized with parenteral typhoid vaccine. It is recommended that a re-immunization dose consisting of 3 vaccine capsules taken on alternate days be given every 5 years under conditions of repeated or continued exposure to typhoid fever (16).

## How Supplied

A single foil blister contains 3 doses of vaccine in a single package.

## Storage

Vivotif® (Typhoid Vaccine Live Oral Ty21a) is not stable when exposed to ambient temperatures. Vivotif® should therefore be shipped and stored between 2 °C and 8 °C (35.6 °F–46.4 °F). Each package of vaccine shows an expiration date. This expiration date is valid only if the product has been maintained at 2 °C–8 °C (35.6 °F–46.4 °F).

## 3.3 Preclinical Evidence

The present study evaluates specific immune responses induced by the commercial vaccine Vivotif®. Safety and efficacy of this vaccine have been demonstrated in several clinical studies and post-marketing studies (please refer to section 3.4). Therefore no preclinical evidence is presented in this protocol.

## 3.4 Clinical Evidence to Date

Results from clinical studies indicate that adults and children greater than 6 years of age may be protected against typhoid fever following the oral ingestion of 3 doses of Vivotif® (Typhoid Vaccine Live Oral Ty21a). The efficacy of the *S. typhi* Ty21a strain has been evaluated in a series of randomized, double-blind, controlled field trials. Suspected typhoid cases, detected by passive surveillance, were confirmed bacteriologically either by blood or bone marrow culture.

The first trial was performed in Alexandria, Egypt with a study population of 32,388 children aged 6 to 7 years. 3 doses of vaccine, in the form of a freshly reconstituted suspension administered after ingestion of 1 g of bicarbonate, were given on alternate days. Immunization resulted in a 95% decrease [95% confidence interval (CI) = 77%–99%] in the incidence of typhoid fever over a 3-year period of surveillance (18).

A series of field trials were subsequently performed in Santiago, Chile, to evaluate efficacy when the vaccine strain was administered in the form of an acid-resistant enteric-coated capsule. The initial trial involved 82,543 school-aged children, and compared 1 or 2 doses of vaccine given one week apart. After 24 months of surveillance vaccine efficacy was 29% (95% CI = 4%–47%) for the single dose schedule and 59% (95% CI = 41%–71%) for the 2-dose schedule (19). A further field trial was performed in Santiago, Chile, involving 109,594 school-aged children (20). Three doses of enteric-coated capsules were administered either on alternate days (short immunization schedule) or 21 days apart (long immunization schedule). Following 36 months of surveillance vaccination resulted in a 67% (95% CI = 47%–79%) decrease in the incidence of typhoid fever in the short immunization schedule group and a 49% reduction (95% CI = 24%–66%) in the long immunization schedule group. After 48 months of surveillance the short immunization schedule resulted in a 69% (95% CI = 55%–80%) decrease in typhoid fever (21). An undiminished level of protection was observed during the fifth year of surveillance. A field trial was next conducted in Santiago, Chile, to determine the relative efficacy of 2, 3 and 4 doses of enteric-coated vaccine administered on alternate days to school-aged children. Relative vaccine efficacy as determined by comparison of disease incidence within the 3 vaccinated groups was highest for the 4 dose regimen (22). The incidence of typhoid fever per 105 study subjects

was 160.5 (95% CI = 130–191) for the 3 dose regimen versus 95.8 (95% CI = 71–121) for the 4 dose regimen ( $p < 0.004$ ). An additional field trial to determine vaccine efficacy was conducted in Plaju, Indonesia, involving 20,543 individuals approximately 3 to 44 years of age (23). Due to logistical considerations 3 doses of enteric-coated capsules were administered at weekly intervals, a schedule known to provide suboptimal protection (20). After 30 months of surveillance vaccine efficacy for all age groups was 42% (95% CI = 23%–57%). Vaccine organisms can be shed transiently in the stool of vaccine recipients (24). However, secondary transmission of vaccine organisms has not been documented. Ty21a has not been isolated from blood cultures following immunization.

At present, the precise mechanism(s) by which Vivotif® confers protection against typhoid fever is unknown. However, it is known that immunization of adult subjects can elicit a humoral anti-*S. Typhi* LPS antibody responses. Taking advantage of this fact, the seroconversion rate (defined as a  $\geq 0.15$  increase in optical density units over baseline determined in an ELISA) was compared in an open study between adults living in an endemic area (Chile) and non-endemic areas (United States and Switzerland) after the ingestion of 3 doses of vaccine. Comparable seroconversion rates were seen between these groups (25).

### Adverse Reactions

More than 1.4 million doses of Ty21a have been administered in controlled clinical trials and more than 150 million doses of Vivotif® (Typhoid Vaccine Live Oral Ty21a) have been marketed world-wide. Active surveillance for adverse reactions of enteric-coated capsules was performed in a pilot study (22) and in a subgroup of a large field trial involving a total of 483 individuals receiving 3 vaccine doses. The overall symptom rates from both studies when vaccinated with capsules were combined and shown to be: abdominal pain (6.4%), nausea (5.8%), headache (4.8%), fever (3.3%), diarrhea (2.9%), vomiting (1.5%) and skin rash (1.0%). Only the incidence of nausea occurred at a statistically higher frequency in the vaccinated group as compared to the placebo group (23). Administration of vaccine doses more than 5-fold higher than the currently recommended dose caused only mild reactions in an open study involving 155 healthy adult males (24).

Post-marketing surveillance has revealed that adverse reactions are infrequent and mild. Adverse reactions reported to the manufacturer during 1991–1995, during which time over 60 million doses (capsules) were administered included: diarrhea (N = 45), abdominal pain (N = 42), nausea (N = 35), fever (N = 34), headache (N = 26), skin rash (N = 26), vomiting (N = 18), or urticaria on the trunk and/or extremities (N = 13). One isolated, non-fatal anaphylactic shock considered to be an allergic reaction to the vaccine was reported.

## 3.5 Dose Rationale

Parameters as dose of vaccine, route of administration, regimen employed and dosage period used in this study, correspond to those used for the administration of the commercial vaccine and are summarized in section 3.2.

## 3.6 Explanation for choice of comparator (or placebo)

Healthy untreated volunteers serve as a control group.

## 3.7 Risks / Benefits

Vivotif® is indicated for immunization of adults and children greater than 6 years of age. This vaccine protects against disease caused by *Salmonella Typhi*, as demonstrated in several clinical studies (refer to section 3.4). Selective immunization against typhoid fever is recommended for the following groups: 1) travellers to areas in which there is a recognized risk of exposure to *S. Typhi*, 2) persons with intimate exposure (e.g. household contact) to a *S. Typhi* carrier, and 3) microbiology laboratorians who work frequently with *S. Typhi*. This vaccine has been shown to be safe; adverse reactions during

administration of enteric-coated capsules of Vivotif® are described in section 3.4. Notably, during a large field trial only the incidence of nausea occurred at a statistically higher frequency in a vaccinated group in comparison with the placebo group.

Despite demonstrated safety of Vivotif®; the vaccine will not be administered to persons during an acute febrile illness. Safety of the vaccine has not been demonstrated in persons deficient in their ability to mount a humoral or cell-mediated immune response, due to either a congenital or acquired immunodeficient state including treatment with immunosuppressive or antimitotic drugs. Therefore the vaccine will not be administered to these persons.

### **3.8 Justification of choice of study population**

The study population was selected considering the prescription indications for Vivotif® (please refer to section 3.2). To minimize the risk of adverse events (AE), a population with an age  $\geq 18$  and  $\leq 50$  years was selected. Additional inclusion criteria important to ensure the welfare of the study subjects were selected and include: No use of an immune modulator in the past year, no use of systemic corticosteroid treatment in the past 30 days and having regular bowel movement. Exclusion criteria important to preserve the health of the subjects included in the study are: positive HIV serology or any immune deficiency, current or planned pregnancy, breastfeeding and obstipation.

## **4. STUDY OBJECTIVES**

### **4.1 Overall Objective**

The purpose of this study is to evaluate the specific immune responses against *Salmonella* porins elicited by the commercial vaccine Vivotif®, as well as the genetic modifications of the live attenuated bacteria contained in the vaccine formulation occurring during vaccination.

### **4.2 Primary Objective**

The primary objective of this study is to evaluate the porins-specific T and B cell immune responses after vaccination with the commercial live attenuated *Salmonella* vaccine Vivotif®.

### **4.3 Secondary Objectives**

The secondary objective is to evaluate the presence of bacteria that bear mutations in their DNA sequences in comparison with bacteria from the original inoculum administered during vaccination.

### **4.4 Safety Objectives**

Not

applicable

## **5. STUDY OUTCOMES**

### **5.1 Primary Outcome**

The primary endpoints of this study are: antibody levels of IgM and IgG specific against porins in serum and IgA in stool, number of porins-specific T cells from blood and amount of porins-specific B cells in blood. These parameters reflect the specific cellular and humoral immune responses induced during vaccination and will allow the study of these types of responses in the present study. Time points for evaluation of primary outcomes are described in section 9.3.

### **5.2 Secondary Outcomes**

The secondary outcomes of this study are the bacteria that bear mutations in their DNA sequences in comparison with bacteria from the original inoculum administered during vaccination. This parameter will be assessed throughout the intervention and follow-up period as depicted in table of the study schedule.

### **5.3 Other Outcomes of Interest**

Not applicable.

### **5.4 Safety Outcomes**

Not applicable.

## **6. STUDY DESIGN**

### **6.1 General study design and justification of design**

This is an open, monocentric, controlled, randomized clinical study conducted with healthy volunteers to evaluate anti-*Salmonella* porins specific immune responses after vaccination with the commercial live attenuated *Salmonella* vaccine Vivotif®. 15 subjects will be vaccinated with Vivotif® and 5 subjects will be left untreated. The study will consist of 7 visits that in total will last 67 days. For a general description of the times in which every assessment will be performed please refer to table 1 in section 9.1. For a description of the procedures performed in the different phases of the study please refer to section 9.3.

The results obtained from this study will reflect the specific cellular and humoral immune responses against *Salmonella Typhi* porins induced during vaccination. The study was designed to have the minimum number of visits possible to increase the probability of study completion by the participants. Enough time of follow up after vaccination is given to analyse the specific anti-porins immune responses in a timeframe that allows collecting solid data.

From the screening of the first participant to the end of follow up, the study will last approximately 3 months. The first participant-in is expected to be in June, 2015 and the last participant-out is expected for September, 2015. End of trial is expected by November, 2015.

### **6.2 Methods of minimising bias**

#### **6.2.1 Randomisation**

Randomization sequence will be created with a 1:3 allocation using random block sizes of 4.

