| Study Product / Intervention:          | Vivotif® (Typhoid Vaccine Live Oral Ty21a) is a live attenuated vaccine for oral administration only. The vaccine contains the attenuated strain Salmonella Typhi Ty21a. One enteric-coated capsule of Vivotif® contains 2.0–10.0x10  colony-forming units (CFUs) of viable S. Typhi Ty21a and 5–50x10  CFUs of non-viable S. Typhi Ty21a bacterial cells.

3 doses of the vaccine are to be administered in alternate days (1, 3 and 5). One capsule is to be swallowed approximately 1 hour before a meal with a cold or lukewarm [temperature not to exceed body temperature, e.g., 37 °C (98.6 °F)] drink.                                                 |
| Control Intervention (if applicable):  | The reference group (n=5) will not be vaccinated.                                                                                                                                                                                                                                                                                                                                                                                                                                                                                                                                                                                                                                                                 |
| Number of Participants with Rationale: | 15 participants in the vivotif ® vaccination group.
5 participants that will not be vaccinated.
Total: 20 participants.
This study is a pilot study; therefore, no sample size calculation was done.                                                                                                                                                                                                                                                                                                                                                                                                                                                                                                     |

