#### **6.2.3 Other methods of minimising bias**

In order to minimize bias block randomization will be used.

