### **7.3 Assignment to study groups**

Block randomization will be used in this study. Random number tables will be generated and assignments will be enclosed in sequentially numbered, opaque, sealed envelopes to designate the 15 subjects that will receive the vaccine and the 5 subjects that will not be administered. After assignment to vaccination/not vaccination groups, the participants will be informed in the second study visit to which group they belong by personnel from the Division of Infectious Diseases and Hospital Epidemiology, Kantonsspital St. Gallen.

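### The block size in 6.2.1 is fixed at four and printed in the protocol, so in this open single-centre trial up to 43.75% of assignments can be deduced; the exposed analysis is the secondary comparison with five controls

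*Protocol*

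**What the plan says.** - Section 6.2.1 (Randomisation): "Randomization sequence will be created with a 1:3 allocation using random block sizes of 4". No second size appears anywhere in the protocol.
- Section 6.2.3 (Other methods of minimising bias) offers the blocking itself as the safeguard: "In order to minimize bias block randomization will be used".
- Section 6.1 describes the trial: "This is an open, monocentric, controlled, randomized clinical study conducted with healthy volunteers". It gives the group sizes as "15 subjects will be vaccinated with Vivotif® and 5 subjects will be left untreated", and the synopsis gives "Total: 20 participants".
- Section 6.2.2 marks blinding as not applicable.
- Section 7.3 provides the concealment: "assignments will be enclosed in sequentially numbered, opaque, sealed envelopes to designate the 15 subjects that will receive the vaccine". It then says that "the participants will be informed in the second study visit to which group they belong by personnel from the Division of Infectious Diseases".
- Section 1 gives recruitment and enrolment to that same division, and section 9.3.2 places enrolment at Visit 2. Section 12.5 gives trial personnel access to the protocol.
- Section 11.4.2 makes the primary analysis a signed rank test of change from baseline, done in each group separately. Section 11.4.3 compares treated with untreated participants by Mann-Whitney U, at baseline and on each person's mean over Visits 5 to 7.

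**The concern.** The wording in 6.2.1 contradicts itself. A random block size needs at least two possible sizes, and only one is named. If the phrase is loose wording for randomly permuted blocks of four, the size is still fixed and the consequence is the same.

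A small fixed block matters when past assignments are visible. Here they are visible to the people who decide who comes next. Once a block's control has been revealed, the rest of that block must be vaccinees. After three vaccinees in a row within a block, the fourth must be a control. Opaque envelopes hide a single assignment, but not one that can be worked out from those already opened.

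What is at stake is selection bias in the controlled comparison. Screening takes place on days -7 to -1, so several eligible volunteers may be waiting at once, with their histories (including recent foreign travel) already taken. Someone who knows the next arm could choose whom to bring forward. With 5 controls, each person is 1/5 = 20% of the comparator.

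**Working it through.** **Inputs.** Allocation 1 control to 3 vaccine and block size 4 (6.2.1); 15 vaccinated and 5 untreated (6.1, 7.3); total 20 (synopsis). The protocol gives no predictability figure.

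**Plan's own figure.** 20/4 = 5 complete blocks. 5 × 3 = 15 vaccine and 5 × 1 = 5 control. This reproduces 15:5.

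**Certain assignments, fixed block of 4.** An assignment is certain when all remaining places in the block must go to the same arm. The control is equally likely to be in each of four positions:

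| Control position | Certain assignments | To vaccine | To control |
|---|---|---|---|
| 1 | 3 | 3 | 0 |
| 2 | 2 | 2 | 0 |
| 3 | 1 | 1 | 0 |
| 4 | 1 | 0 | 1 |

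Mean per block = (3 + 2 + 1 + 1)/4 = 1.75, and 1.75/4 = 43.75%. Over five blocks, 5 × 1.75 = 8.75 of 20. By arm: vaccine 5 × 6/4 = 7.5 of 15; control 5 × 1/4 = 1.25 of 5.

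**How much this adds to knowing the ratio.** Always guessing vaccine is right 75% of the time. With blocks of four, the best guess is right with probability 0.75 at each of places 1 to 3 and 1 at place 4: (3 × 0.75 + 1)/4 = 81.25%, or 16.25 of 20.

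**Alternatives, by the same enumeration.**

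| Scheme | Certain, of 20 | Share | Best guess right |
|---|---|---|---|
| Fixed blocks of 4 | 8.75 | 43.75% | 81.25% |
| Sizes 4 and 8, hidden order | 3.08 | 15.4% | 79.7% |
| One permutation of 15 and 5 | 2.81 | 14.1% | 77.0% |

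The 4/8 row assumes that the 8 orderings of 4s and 8s summing to 20 are equally likely, and that staff know the possible sizes but not the order. For the single permutation, 15/6 + 5/16 = 2.81.

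**Balance if recruitment stops early.**
- *Fixed blocks of 4:* exactly 2 controls after 8 participants and exactly 3 after 12.
- *Hidden 4/8 mix:* 2 of the 8 orderings have a block of 8 straddling participant 8, and 2 of the 8 straddle participant 12. Half-way through such a block there are 0 controls with probability C(4,2)/C(8,2) = 6/28, and 2 controls with the same probability. The count is therefore one below the target with probability (2/8)(6/28) = 5.4%, and one above with the same probability. It is 1 to 3 after 8 and 2 to 4 after 12.
- *Single permutation:* 0 or 1 control after 8 has probability (792 + 3960)/15504 = 31%. After 12 it is (56 + 840)/15504 = 5.8%.

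**The case against.** Several points on the other side are sound.

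- **43.75% is a ceiling.** It requires enrolling staff to know the block size and to have seen every earlier assignment in the block. The study runs about 3 months from first screening to the end of follow-up, and each participant takes 67 days. At about 90 days for 3 months, that leaves roughly 90 - 67 = 23 days to bring in 20 people. Overlapping screening and Visit 2s close together are likely, and both reduce what can be deduced.
- **Most of the certainty is about the common arm.** Of 8.75 certain assignments, 7.5 are to vaccine, already the default guess. The best guess improves only from 75% to 81.25%.
- **The hypothesis in 11.1 and the primary test in 11.4.2 are within person.** They do not use the control arm to judge vaccinees. The trial is a 20-person pilot, and the immunological assays are run by an institute separate from the recruiting division.
- **Nothing in the protocol suggests that staff would steer anyone.** Recent oral *Salmonella* vaccination and recent *Salmonella* gastrointestinal infection are exclusions, which narrows the scope for selection. Nor does the protocol say that the recruiting division prepares the list.

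These points limit the size of the problem. They do not answer it: the text fixes one disclosed size, and the protocol itself puts disclosure and enrolment in the same hands. The baseline comparison of arms in 11.4.3 is a weak check at 15 against 5.

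A reader might infer that about 44% of assignments will in fact be known, that concealment is wholly undone, or that the primary result is biased. The documents support none of these. Even at the ceiling 56.25% of assignments are not certain, and the primary analysis is within group.

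**Conclusion.** The point holds in a limited form. Section 6.2.1 calls a single size random, and the block it fixes is small, known and used in an open trial. Up to 43.75% of assignments (8.75 of 20 expected) are deducible. This assumes complete blocks of four, a block size known to enrolling staff, and full disclosure of earlier assignments in the block. The true figure is lower by an amount the protocol does not allow one to calculate.

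The harm falls on the treated-versus-untreated comparison in 11.4.3, the only planned between-group test. Section 6.2.3 gives the wrong reason for blocking: blocking keeps the arms balanced over time, but with a known small block in an open trial it weakens concealment. This should be corrected before the first participant is enrolled, though it does not put the primary analysis in doubt.

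**What to change.** 1. **Section 6.2.1:** use block sizes of 4 and 8 in random order, totalling 20, at one control to three vaccine. Keep the sizes and their order in a document outside the protocol and withhold them from enrolling staff. State that the list is prepared outside the recruiting division, for example by the Clinical Trials Unit, which section 1 already involves.
2. **Section 6.2.3:** name concealed allocation with undisclosed, varying blocks as the safeguard, instead of blocking itself.

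This cuts certain assignments from 43.75% to about 15% (equally likely orderings assumed) and still ends at 15:5. The direct cost is a new list and a short wording change. The downside is slightly looser balance if recruitment stops mid-block: one control more or fewer than target in about 11% of cases (2 × 5.4%) at 8 or at 12 participants.

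A single permutation of 15 and 5 would reach 14.1%, but it risks 0 or 1 control if recruitment stops early (31% at 8 participants, 5.8% at 12). Section 2.9 lists insufficient recruitment as a ground for termination, so the mixed blocks are the better trade.
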